### Data collection, monitoring and interim analysis

Trained researchers will be responsible for data collection. The principal investigator (PI) will be responsible for double-checking the collected data and input data into the study database. The quality of data will be guaranteed by locking the variables’ input range and random checking for quality 5% of patient data at each interim analysis and final analysis database.

The collected data will include age, race, gender, weight, hospital and ICU admission dates, main ICU diagnosis, cirrhosis etiology, transplant list status, comorbidities, Simplified Acute Physiology Score (SAPS 3) [44], Sequential Organ Failure Assessment (SOFA) score [45], Model for End-stage Liver Disease (MELD) score [46], transfusion of blood products in the previous 24 h and 24 h after CVC, procedure time, procedure indication, catheter type, number of attempts, insertion site, inserter, elective/emergency insertion, hemoglobin, hematocrit, PT, aPTT, platelet count, serum fibrinogen, ionized calcium, pH, peripheral temperature, ROTEM® parameters (CT, CFT, α angle, MCF and A10), type and quantity of transfused blood products for the procedure, adverse events related to the procedure and transfusion, when indicated, length of ICU and hospital stay and mortality at day 28.

An independent Data Safety Monitoring Board (DSMB) will conduct two interim analyses after the enrollment of 55 and 110 participants. The Lan-DeMets alpha spending function method will be used to determine statistical differences between groups [47]. After DSMB assessment, a report will be generated recommending whether the trial should continue or stop due to efficacy or harm. The final decision to stop the trial will be held by the PI together with the POCKET Trial Investigators. An independent audit will be conducted every 6 months after recruitment of the first patient. Every serious adverse event will be immediately reported to the Ethics Committee and the DSMB, and minor adverse events will be enlisted and periodically released. Every protocol amendment will be subject to approval from the local Ethics Committee.

### Statistical analysis plan

All analyses will be performed as intention-to-treat. Categorical variables will be summarized as absolute and relative frequencies. Normality will be tested with the Kolmogorov-Smirnov test. Accordingly, continuous variables with normal distribution will be summarized as mean ± SD, or median and interquartile range (IQR) in case of non-normal distribution.

Comparisons between groups of continuous variables will be performed with one-way analysis of variance (one-way ANOVA) followed by Tukey’s test for multiple comparisons (for normally distributed variables), or the Kruskal-Wallis test followed by the Mann-Whitney *U* test (for non-normally distributed variables). Proportions between groups will be analyzed with the chi-square test or Fisher’s exact test, as appropriate.

All binary outcomes will be analyzed using a generalized linear model with binomial distribution and logit link function followed by pairwise comparisons adjusted by Bonferroni correction for multiple comparisons. Pairwise comparisons will be presented as odds ratio (OR) along with 95% confidence interval (95% CI), which will be calculated by logistic regression.

A survival curve will be performed with the Kaplan-Meier estimator and the log-rank test will be used to compare groups. To assess time-to-event (28-day mortality), an unadjusted Cox proportional hazards regression model will be performed. The hazard ratio (HR) with its respective 95% CI will be reported.

Prespecified subgroup analysis for the primary outcome will be presented as a Forest plot, and will include the presence of hypothermia (<35 °C), SAPS 3 score (≥50 points) and MELD score (≥25 points). Interaction between groups and each covariate will be assessed by multivariate logistic regression.

Two-tailed tests will be used and when *p* < 0.05, the test will be considered statistically significant. To account for multiple comparisons (Coagulogram-based versus Thromboelastometry-based, Coagulogram-based versus Restrictive and Thromboelastometry-based versus Restrictive), the α level will be adjusted to 0.0167.

We will make maximum effort to reduce missing data. We will use the multiple imputation method to handle missing data when necessary. The Statistical Package for the Social Sciences version 22.0 (IBM Inc., Chicago, IL, USA) will be used for statistical analyses. GraphPad Prism version 6.07 (GraphPad Software Inc., La Jolla, CA, USA) will be used for graph plotting.

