### Laboratory procedures

Before a CVC, every included patient will be submitted to blood sampling for SCTs (PT, INR, aPTT and platelet count), ROTEM® analysis, serum fibrinogen, hemoglobin, hematocrit, ionized calcium and arterial pH. Blood samples of 5 mL will be obtained directly from a peripheral vein by applying a light tourniquet to avoid blood stasis, or from a central venous line after discarding the first 5 mL of blood (in the case of an indication for a second CVC, e.g., hemodialysis catheter), or from an arterial line. Blood samples for SCTs, ROTEM® and fibrinogen will be conditioned in citrate tubes (3.2%; Sarstedt Monovette®, Wedel, Germany) and processed immediately. Blood samples for hemoglobin level, hematocrit and platelet count will be conditioned in 2.6-mL tubes containing EDTA KE (Sarstedt Monovette®, Wedel, Germany).

Thromboelastometry analysis (ROTEM® delta, Pentapharm Co., Munich, Germany) will be performed by pipetting 300 μL citrated whole blood and 20 μL 0.2-M calcium chloride (CaCl_2_) with specific activators into a plastic cup [38]. Extrinsically activated (EXTEM), intrinsically activated (INTEM), and fibrinogen polymerization (FIBTEM) assays will be performed. ROTEM® analysis will run for up to 60 min. The parameters coagulation time (CT; s), clot formation time (CFT; s), maximum clot firmness (MCF; mm), alpha angle (α; degrees) and amplitude at 10 min (A10; mm) will be recorded [38].

The EXTEM assay contains a preparation of human recombinant tissue factor, which activates the coagulation cascade and can assess coagulation status via CT_EXTEM_, CFT_EXTEM_ and MCF_EXTEM_ [27]. The FIBTEM assay uses cytochalasin D which is a potent platelet inhibitor and serves to evaluate fibrinogen function and fibrin polymerization [27]. The A10 is a surrogate marker of MCF and can predict coagulopathy with high sensitivity and specificity (1.0 and 0.7, respectively) with the advantage of a faster evaluation of coagulation disorders [39].

Prothrombin time, INR and aPTT (ACL TOP 700 system, Instrumentation Laboratory, Bedford, MA, USA), serum fibrinogen (Clauss method) and platelet count (Sysmex® XN-Series, Sysmex Corporation, Lincolnshire, IL, USA) will be performed according to the hospital’s standard analytical methods.

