**Fig. 1 Fig1:**
[figure not shown]
Coagulogram-based blood transfusion protocol. *INR* international normalized ratio; *aPTT* activated thromboplastin time; *FFP* fresh frozen plasma

Accordingly, if INR ≤1.5, aPTT ≤50 s, platelet count ≥50,000/μL and serum fibrinogen ≥150 mg/dL, no transfusion is indicated. Otherwise, if INR >1.5 or aPTT >50 s, FFP is transfused at 10 mL per kg of body weight; and/or if platelet count <50,000/μL, 1 unit per 10 kg of body weight of random platelets (up to 10 units) or 1 unit of apheresis platelets is transfused; and/or if serum fibrinogen <150 mg/dL, 1 unit per 10 kg of body weight of cryoprecipitate is transfused (up to 10 units).

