### Study endpoints

The primary efficacy endpoint is the proportion of patients transfused with any blood product (i.e., FFP, platelets or cryoprecipitate) prior to CVC. The primary safety endpoint is the incidence of major bleeding within the first 24 h after catheter insertion. Major bleeding was defined according to the HEME tool [41]. According to the HEME tool, major bleeding is defined as overt bleeding with any of the following (in the absence of other causes): decrease in hemoglobin of 20 g/L or more, transfusion of 2 or more units of RBC with no increase in hemoglobin level, decrease in systolic BP by 10 mmHg or more while the patient is sitting up, spontaneous decrease in systolic BP of 20 mmHg or more or increase in heart rate by 20 bpm or more; bleeding at any one of the following sites: intracranial, intraspinal, intraocular, pericardial, retroperitoneal or intraarticular; or wound-related bleeding requiring an intervention.

The secondary efficacy endpoints will be: the proportion of patients transfused with each blood component and the infused volume of each blood component, hemoglobin and hematocrit levels before and up to 24 h after CVC, costs associated to blood product transfusion and laboratory tests, ICU and hospital length of stay, and ICU, 28-day and hospital mortality. Secondary safety endpoints will include: the incidence of minor bleeding complications (i.e., oozing or hematoma with no criteria for major bleeding) and the proportion of patients transfused due to bleeding within the first 24 h after CVC, and the incidence of acute transfusion-related adverse events (i.e., transfusion-associated cardiac overload, acute hemolytic transfusion reactions, anaphylactic reactions, febrile nonhemolytic reactions and urticarial reactions). The transfusion of bleeding patients after CVC will follow the Hospital Israelita Albert Einstein institutional transfusion protocol. Accordingly, if INR >1.5 or aPTT >32 s, FFP (10 mL per kg) is administered. If serum fibrinogen <150 mg/dL, cryoprecipitate (1 unit per 10 kg) or fibrinogen concentrate (2 to 4 g) is administered. If the platelet count <50 x 10^3^/mm^3^, random platelets (1 unit per 10 kg) or apheresis platelets (1 unit) are administered. Correction of hypothermia (axillary temperature ≥35 °C), hypocalcemia (ionized calcium ≥1.14 mmol/l) and acidosis (pH ≥7.31) is always recommended.

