### Randomization, allocation and blinding

Allocation sequence with random numbers will be computer-generated using random, varied size blocks and stratification by severe renal failure (i.e., hemodialysis program). The randomization sequence will be stored in individually separated and sequentially numbered opaque, sealed envelopes and kept secured in a locker with restricted access (centralized at ICU pharmacy). After the consent term is signed and coagulation tests collected, patients will be randomly assigned to study groups with an allocation ratio of 1:1:1.

Allocation concealment will be preserved by holding randomization sequence disclosure until the consent term is signed and coagulation tests collected. Patients will be enrolled by an on-call recruiter, and assignment to intervention will be provided by an independent researcher, who will be the only one to know which intervention the patient will be assigned to. The research subjects, central venous catheter inserter and outcome assessors will be blinded to the assigned intervention and bleeding will be assessed by the use of the HEME tool [41] immediately after CVC and 24 h after the procedure. The catheter inserter is not directly responsible for care of the patient included in the trial and will not have access to the patient’s chart. In case of major bleeding or serious transfusion-related adverse reaction, unblinding to the attending physician is anticipated.

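### Hemoglobin and hematocrit are assigned to tests that cannot use the pre-randomization value or the dialysis stratum; ANCOVA would be more precise at no cost (minor, secondary endpoint)

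*Protocol article*

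**What the plan says.** All places are in the protocol article.

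- **Statistical analysis plan.** One rule covers all continuous variables: "Comparisons between groups of continuous variables will be performed with one-way analysis of variance", followed by Tukey's test. For non-normal data it is "the Kruskal-Wallis test followed by the Mann-Whitney" test. No covariate is named.
- **Study endpoints.** The secondary efficacy endpoints include "hemoglobin and hematocrit levels before and up to 24 h after CVC". Whether the later level or the change is compared is not stated.
- **Laboratory procedures.** "Before a CVC, every included patient will be submitted to blood sampling for SCTs", and the same list includes hemoglobin and hematocrit.
- **Randomization, allocation and blinding.** "After the consent term is signed and coagulation tests collected, patients will be randomly assigned to study groups with an allocation ratio of 1:1:1". The sequence is stratified by severe renal failure, meaning a hemodialysis program.
- **Coagulogram-based group.** "if INR >1.5 or aPTT >50 s, FFP is transfused at 10 mL per kg of body weight". The restrictive arm gives the same volume only above an INR of 5.0, and the thromboelastometry arm only when the EXTEM clotting time exceeds 80 s.

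**The concern.** The endpoint is a before-and-after measure. The earlier value is listed with the coagulation tests that are collected before allocation, so it is a proper baseline covariate. The stratification factor is also known for every patient. One-way ANOVA and Kruskal-Wallis can use neither as a covariate. With about 55 patients per arm, discarding a strongly prognostic baseline widens the confidence intervals on this endpoint for no benefit.

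A second matter concerns reading the result, not the test. The arms receive different amounts of plasma by design, and plasma dilutes hemoglobin. An arm difference could therefore appear with no difference in blood loss.

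**Working it through.** **The plan's own figures.** None is given for hemoglobin or hematocrit. The arm size used below is the stated 55. Its starting point reproduces for 90% against 65%, two-sided alpha 0.05 and power 0.80: (1.96 × √(2 × 0.775 × 0.225) + 0.842 × √(0.09 + 0.2275))² / 0.25² = 42.6, so 43. Then 43 + 8 + 4 = 55.

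**Precision.** Let r be the before-after correlation, with equal variances. The documents give no r, so a range is assumed. Relative to an ANOVA on the post value (variance 1), an ANOVA on the change has 2(1 − r) and ANCOVA has 1 − r². ANCOVA relative to the change is (1 − r²) / (2(1 − r)) = (1 + r)/2.

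| r (assumed) | Change | ANCOVA | ANCOVA ÷ change | ANCOVA patients per arm that match 55 by post-value ANOVA |
|---|---|---|---|---|
| 0.6 | 0.80 | 0.64 | 0.80 | 35 |
| 0.7 | 0.60 | 0.51 | 0.85 | 28 |
| 0.8 | 0.40 | 0.36 | 0.90 | 20 |
| 0.9 | 0.20 | 0.19 | 0.95 | 10 |

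Minimum detectable pairwise difference, with an assumed SD of 15 g/L, alpha 0.05 and power 0.80: 2.80 × 15 × √(2/55) = 8.0 g/L for post-value ANOVA. Multiplying by √(1 − r²) gives 6.4, 5.7, 4.8 and 3.5 g/L for ANCOVA at r = 0.6, 0.7, 0.8 and 0.9. The contribution of the dialysis stratum is not included.

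**Dilution.** The fall in a plasma recipient is Hb × v/(BV + v), where v is the part of 10 mL/kg still in the circulation and BV is blood volume. With BV 70 mL/kg, full retention and Hb 90 g/L (all assumed): 90 × 10/80 = 11.3 g/L. Over BV 60 to 80 mL/kg, retention 25% to 100% and Hb 80 to 100 g/L, the range is:

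- lowest: 80 × 2.5/82.5 = 2.4 g/L
- highest: 100 × 10/70 = 14.3 g/L

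Only the difference in exposure between arms shifts the comparison:

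- At the planned 25 points, if all of it were plasma: 0.25 × 2.4 to 0.25 × 14.3 = 0.6 to 3.6 g/L.
- At an assumed 75 points: 1.8 to 10.7 g/L.

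**Does baseline adjustment remove the shift?** No. Three-arm simulations were run with 55 per arm, SD 15 g/L, r = 0.8, an 11 g/L fall in recipients and no bleeding at all. The mean shift was practically the same under all three analyses: about 2.8 g/L for plasma in 90% against 65%, and about 7.7 g/L for 90% against 20%. In the first case the global test rejected in about 13–15% (post value), 27–29% (change) and 29–33% (ANCOVA) of runs. In the second it rejected in about 75–81%, 98–99% and 99% or more. A more precise analysis sees dilution more clearly. With no fall, every method rejected in about 5–6% of runs.

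**The case against.** **The stated analysis is valid, and a condensed article may leave model detail to the analysis plan.** Validity stands: one-way ANOVA in a randomized trial estimates the total effect of each strategy without bias. But the article does not leave the method open. It names tests that exclude covariates for every continuous variable, so proposing a better one is not a complaint about missing detail.

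**The baseline may be used after all, through the change score.** This stands in part. A reader might infer from the ANOVA wording that the baseline is ignored and that half or more of the information is lost. The article does not define the variable compared, so the large saving holds only if post values are compared. ANCOVA is at least as precise either way.

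**The baseline is drawn at the wrong time.** A reader might infer this because the sample precedes plasma. The documents do not support it as a fault. A pre-randomization value is the correct baseline, whereas one drawn after transfusion would be affected by treatment. Dilution lies in the later value whichever analysis is used.

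**The primary safety endpoint is tilted towards the new strategies.** A reader might infer this because a 20 g/L hemoglobin fall is one route to major bleeding. The definition under Study endpoints counts such a fall only with overt bleeding and no other explanation, and dilution is another explanation. In the ranges above, dilution alone stays below 20 g/L. The assumed 90% control transfusion rate is for any product, not plasma alone. What remains is that assessors blinded to the arm may find it hard to recognise dilution as the explanation. That is possible, but nothing in the documents allows it to be sized.

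**The protocol never says it will read hemoglobin as bleeding.** Correct. It files hemoglobin under efficacy and assesses bleeding separately, so the dilution point is a caution and not an error.

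**Conclusion.** The point holds as a minor one on a secondary endpoint. The named tests cannot use the pre-randomization value or the dialysis stratum, and ANCOVA would be more precise at no cost. Against a post-value ANOVA it leaves 51% to 36% of the variance at r = 0.7 to 0.8. Against a change-score ANOVA it saves about 5% to 20% at r = 0.6 to 0.9. The correlation and SD are assumptions. That hemoglobin is drawn before allocation is inferred from its place in the same sampling list as the coagulation tests.

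The dilution point survives only as a caution on interpretation. Its size depends on assumed blood volume, plasma retention and the true difference in plasma use. It does not show that the analysis or the major bleeding endpoint is biased.

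**What to change.** 1. State the variable and the model: post-catheterization hemoglobin, and likewise hematocrit, analysed by ANCOVA with the pre-catheterization value and the dialysis stratum as covariates. Pairwise contrasts of adjusted means take the multiplicity control already planned.
2. Add one sentence: a difference between arms in hemoglobin or hematocrit will be reported alongside infused plasma volume by arm and will not by itself be interpreted as blood loss.
3. Optional: a sensitivity analysis of major bleeding that leaves out events classified by the hemoglobin criterion alone.

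The cost is wording in the analysis plan. Hemoglobin, hematocrit, and the type and quantity of products are already on the data collection list, and the stratum is known from randomization. No visit, sample or treatment rule changes, and the sample size is unaffected.

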### Costs analysis

Transfusion and laboratory test costs will be assessed. For the analysis of the costs of laboratory tests, we will include the total cost of the test(s) (i.e., ROTEM® or SCTs), which will guide the blood transfusion. The unit cost information regarding blood products and coagulation tests will be obtained from the blood bank and main laboratory of Hospital Israelita Albert Einstein.

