## Discussion

Our trial is designed to compare three protocols to guide transfusion of blood components prior to CVC in critically ill patients with chronic liver failure. We hypothesized that restricted and thromboelastometry-guided transfusion protocols would be safe and significantly reduce empirical transfusion of blood products in cirrhotic critically ill patients. By reducing transfusion rates, these strategies would also reduce transfusion-related complications and costs. This would help to provide quality evidence for reduction of empirical transfusion of critically ill patients with coagulopathy in clinical practice.

One main focus of our trial is that the transfusion protocols used are based on a comprehensive assessment of coagulation, which includes the contribution of coagulation factors, platelets and fibrinogen. Most randomized trials published so far have relied on a specific aspect of coagulation and a specific blood product transfusion (e.g., FFP transfusion according to PT/INR) [48, 49]. Furthermore, fibrinogen is one of the most important coagulation factors [50], and we believe that including the evaluation of hypofibrinogenemia or dysfibrinogenemia would result in a more detailed understanding of coagulation status and, therefore, help in further prevention of bleeding. Additionally, we will use wide inclusion criteria, accounting for emergency insertions, active bleeding and use of antiplatelet aggregation agents making the case-mix of patients more similar to critical care practice.

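### Costs are routed by a normality test to medians and rank tests, which do not estimate the mean cost difference behind the cost hypothesis; separately, raw length of stay counts an early death as a short stay

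*Protocol article*

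**What the plan says.** All from the protocol article.

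- **Statistical analysis plan.** The rule starts with a pre-test: "Normality will be tested with the Kolmogorov-Smirnov test". Variables that pass get mean ± SD and one-way ANOVA with Tukey's test. The others are summarised by "or median and interquartile range (IQR) in case of non-normal distribution" and compared by the second route, "or the Kruskal-Wallis test followed by the Mann-Whitney" U test. The Kaplan-Meier, log-rank and Cox methods are for survival and 28-day mortality, not for stay.
- **Study endpoints.** The secondary efficacy endpoints include "costs associated to blood product transfusion and laboratory tests, ICU and hospital length of stay, and ICU, 28-day and hospital mortality".
- **Costs analysis.** It opens with "Transfusion and laboratory test costs will be assessed", then says which tests are counted and where unit costs come from. It names no summary measure or test, so the general rule is the only stated method for cost.
- **Discussion.** The authors expect that "these strategies would also reduce transfusion-related complications and costs". The Discussion paragraph of the Abstract also hypothesises lower costs.

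**The concern.** A claim that a strategy reduces costs is a claim about money spent: patients treated times mean cost per patient. Transfusion cost is zero for an untransfused patient and right-skewed for the rest, so the normality rule will tend to move it to medians and rank tests. Neither estimates the mean difference. The cost conclusion could then rest on a statistic that answers another question, and under some cost patterns it could suggest a saving where mean spending is equal.

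Length of stay has a different problem. Patients are critically ill and mortality is itself an endpoint, yet the article gives no rule for the stay of a patient who dies. An early death enters as a small number of days, which reads as a good result. A strategy with more early deaths could appear to shorten stay. This matters in a trial that also hypothesises that less transfusion is safe.

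**Working it through.** **Inputs from the article.** Planned transfusion rate is 90% in the control arm, with an absolute reduction of 25 points, so 90% − 25% = 65% in each experimental arm and 35% with no transfusion cost. Pairwise α is 0.0167. There are 55 patients per arm. The starting figure of 43 reproduces: with p̄ = 0.775, n = [1.96·√(2·0.775·0.225) + 0.842·√(0.9·0.1 + 0.65·0.35)]² / 0.25² = 42.6, rounded up to 43; then 43 + 8 + 4 = 55. The point does not depend on that calculation; it only sets n for the simulations.

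**Assumptions.** The article gives no prices, spreads, lengths of stay or death rates. All such values below are assumed.

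**Step 1. Will costs leave the normal branch?** Cost = fixed test cost (50) + lognormal transfusion cost (log-mean 6, log-SD 0.3 or 0.6) in those transfused; n = 55, 1000 runs. Share of runs rejecting normality at 0.05:

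| Transfused | Lilliefors form | Uncorrected Kolmogorov-Smirnov |
|---|---|---|
| 90% | 54–65% | 1–13% |
| 65% | 98.5–100% | 63–94% |
| 30% or 10% | about 100% | about 100% |

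The move to ranks is very probable at the planned experimental rate and near certain below it. In the control arm taken alone it is uncertain.

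**Step 2. What do the rank route and the mean each report?** 4000 runs, 55 per arm, lognormal transfusion cost with log-SD 0.4, Mann-Whitney and Welch t at 0.0167.

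- *Equal means, 90% v 25% transfused.* Test cost 20 and mean transfusion cost 100 give 20 + 0.90·100 = 110. Test cost 60 and mean transfusion cost 200 give 60 + 0.25·200 = 110. Mann-Whitney was significant in 76.6% of runs and Welch in 2.2%. The average median difference was 47 units and the average mean difference about 0.
- *Equal means, 90% v the planned 65%.* First arm as above; the second has test cost 60 and mean transfusion cost 50/0.65 = 76.9, so 60 + 50 = 110. Mann-Whitney was significant in 1.7% and Welch in 1.4%: no false signal.
- *Unequal means, 40% v 15% transfused.* With test cost 20 and mean transfusion cost 100 in both, the means are 60 and 35, a difference of 25. The average median difference was about 3, because both medians sit mostly at the test cost. Mann-Whitney was still significant in 70% of runs (Welch 62%).

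The rank test can therefore detect a shift, but the statistics reported with it can miss the size of the saving, and in some patterns its existence.

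**Step 3. Length of stay.** Survivors' stay is the same in both arms (lognormal, mean 20 days); deaths occur at a mean of 5 days; log-SD is 0.6 for both. Mean stay = 20·(1 − d) + 5·d for mortality d. At d = 0.30 this is 15.5 days, at 0.50 it is 12.5 and at 0.60 it is 11.0. With nobody's stay shortened among survivors:

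| Mortality | Mean stay shorter by | Median shorter by | Mann-Whitney significant | Welch significant |
|---|---|---|---|---|
| 30% v 30% | 0 | about 0 | 1.8% | 1.4% |
| 30% v 50% | 3.0 days | 3.8 days | 22% | 12% |
| 30% v 60% | 4.5 days | 5.3 days | 52% | 32% |

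The means shift as well as the medians, so the stay problem does not come from the normality rule.

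**The case against.** Three stronger readings are tempting, and the document supports none of them.

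1. *Rank tests cannot show a change in cost.* They can. With 22 of 55 v 3 of 55 transfused at one common cost, Mann-Whitney gives p ≈ 0.00002. The plan also reports the IQR, and there the upper quartile is the transfusion cost in one arm and zero in the other. What is missing is an estimate of the mean difference.
2. *The median transfusion cost will be zero.* Not at the planned 90% and 65%, where more than half of each arm is transfused. It is zero only if fewer than half are, which the article does not assume.
3. *The normality switch makes early deaths look like short stays.* The ANOVA branch does the same (Step 3). Stay needs a separate rule whichever branch applies.

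It can also be said that a condensed article may leave the cost summary to a fuller plan, and that the equal-means example uses prices chosen to cancel. The second is correct: the example shows what can happen, not what is likely. The first carries less weight, because the article does state a rule for continuous variables and gives cost no exception.

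On stay, no hypothesis claims a shorter one, and the endpoints already list mortality alongside: "ICU and hospital length of stay, and ICU, 28-day and hospital mortality". A misleading result needs mortality to differ between arms, which nothing in the article suggests. At 30% v 50% the mortality comparison has expected z = 0.20/√(0.4·0.6·2/55) = 2.14 against a critical value of 2.39, so about 40% power. It would be significant more often than the stay comparison (22%). That makes the problem smaller, but the stay result remains hard to interpret.

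**Conclusion.** The point holds in a limited form. The one stated rule for continuous variables will very probably take costs to median (IQR) and rank tests in arms with a sizeable untransfused share. Those methods can reach significance but do not estimate the difference in mean cost that the hypothesis is about. Under some patterns they can point to a saving when means are equal: 77% v 2% of runs in the assumed 90% v 25% case, but no such signal in the assumed case at the planned 65%. How far this matters depends on unit prices and transfusion rates that the article does not give.

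The stay problem is separate and holds under both branches. It has consequences only if mortality differs between arms; at an assumed 30% v 50%, the arm with more deaths looks 3 to 4 days shorter.

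This is a minor improvement, confined to secondary endpoints.

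**What to change.** **Cost.** State before analysis that, whatever the normality test shows, arithmetic mean cost per patient will be compared between arms, with a bootstrap confidence interval for each pairwise difference. Keep median (IQR) as description.

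**Length of stay.** State a rule that accounts for death: either time to discharge alive with death as a competing event, or days alive and out of the ICU (and hospital) to day 28 with death scored zero. Show mortality beside it and keep raw stay as description.

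**What it costs.** A little more analysis work. Product quantities, unit costs, admission dates, stays and day-28 mortality are already to be collected. The drawback is that days alive and out of the ICU or hospital mix stay with death, so they must be read with the mortality results.
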